## Abstract

**Background:**

Preterm birth is the most common cause of neonatal morbidity and mortality. Tocolytics are considered a standard treatment for women with threatened preterm delivery to allow time for maternal steroid administration and transfer to referral centers with neonatal intensive care units. However, there is controversy about the best tocolytic therapy to be considered as the first choice. The aim of this study is to compare the tocolytic effectiveness and tolerability of combination therapy with nifedipine and indomethacin versus nifedipine monotherapy among Sudanese women with preterm labor (PTL) as well as to compare the possible neonatal outcomes associated with each drug.

**Methods/design:**

This is a randomized controlled clinical trial to be conducted in the Medani Maternity Hospital, Sudan. Women aged 18–40 years that are diagnosed with preterm labor and have a gestational age between 25 and 34 weeks will be eligible to participate in this trial. The diagnosis of threatened PTL is defined as persistent uterine contractions “(four contractions every 20 min or eight contractions every 60 min)” with cervical changes “(cervical effacement ≤80% or cervical dilatation >two cm)”. Patients will be eligible regardless of the presentation of the fetus. It will be randomly decided whether participants receive nifedipine/indomethacin combination therapy or nifedipine monotherapy. The primary outcome is the number of women who do not deliver and do not need alternative tocolytic drug (terbutaline). The secondary outcome is an estimated association with neonatal morbidity and mortality. The sample size will be 117 subjects in each arm of the study, according to a type I error of 0.05 and a study power of 80%.

**Discussion:**

We expect higher effectiveness of the combination indomethacin/nifedipine tocolytic therapy compared with nifedipine monotherapy. We plan to suggest this combination therapy as the best option for postponing PTL.

**Trial registration:**

Clinical trial registration: PACTR202004681537890, date of registration: March 8, 2020.

**Supplementary Information:**

The online version contains supplementary material available at 10.1186/s12884-021-03951-x.

## Background

Preterm labor (PTL) can be described as the presence of regular uterine contractions that result in cervical dilatation prior to the 37th week of pregnancy and is one of the leading causes of death and serious adverse events in newborns [1, 2]. PTL is associated with 50–75% of neonatal mortality and 50% of neonatal morbidity worldwide [3, 4]. PTL is also associated with economic burden due to the high requirements of neonatal intensive care units and socioeconomic disadvantages to the affected patients related to disruptive life events [5, 6]. PTL occurs in approximately 4–15% of all pregnancies, and these percentages have increased in recent years [5, 7]. The rates of PTL vary according to countries and regions; they are approximately 5% in some northern European countries but over 15% in some countries of sub-Saharan Africa and Asia [8]. In Sudan, preterm births occur in 3.8% of all pregnancies, and the majority (81.0%) of these preterm births are spontaneous [8, 9].

PTL-associated morbidity and mortality rates are inversely related to gestational age at delivery. Although 50% of PTL occurs after gestational week 35, the associated morbidity and mortality occurs before this time in 99% of cases [10]. Using tocolytics in women as labor-inhibiting agents could postpone delivery by inducing myometrium relaxation [11]. It has been shown that survival rate increases by 3% for every 24 h of labor delay, which allows for further neonatal rescue intervention and the administration of alternative treatments, such as antenatal corticosteroids, during the extended period until delivery [12, 13]. Several tocolytic classes are commonly used, including ritodrine hydrochloride, prostaglandin antagonists indomethacin and ketorolac, the β-adrenoceptor agonist ritodrine, magnesium sulfate, the oxytocin receptor antagonist atosiban, the calcium channel-blocking agent nifedipine, and others. These medications tend to be used due to their unique mechanisms of action. However, each one has its own profile, which includes adverse effects and methods of administration [14]. There are still controversies regarding their effectiveness and associated adverse events. A randomized clinical trial that investigated the effect of nifedipine versus placebo in the treatment of preterm contractions reported that nifedipine was more efficient compared with the placebo [15]. It has been suggested that combination therapy could be a viable option for the prevention of PTL [16]. A previous trial has shown promising results regarding the superiority of nifedipine and indomethacin as a combined therapy for PTL [17]. However, there was no significant difference in terms of efficacy and safety profile when three tocolytic agents (indomethacin, nifedipine and magnesium) were evaluated for the treatment of PTL [18, 19]. Importantly, none of these studies were conducted in Africa.

The aim of this study is to compare the tocolytic effectiveness and tolerability of a combination therapy consisting of nifedipine and indomethacin versus nifedipine monotherapy among Sudanese pregnant women with PTL as well as to compare the possible neonatal outcomes associated with each drug.

### Aims of the study

The primary objective of this study is to record the number of women at risk of PTL with a gestational age between 25 and 34 weeks who do not deliver and do not need alternative tocolytic drug (for 48 h) of the combined tocolytic agents nifedipine and indomethacin or the nifedipine monotherapy in delaying delivery for 48 h in women. The secondary objective is to compare the effectiveness of the two mentioned therapies in regard to improvements in neonatal outcomes among the same study groups. The outcomes include neonatal mortality and morbidity.

(SPIRIT Checklist Statement) Additional file 1.

**Table 1 Tab1:** Study timetable and activities

Phase	Duration	Activities
**Phase 1**	**6 months**	1- Preparation of the study team
		2- Preparation of the study drugs
		3- Design of the study forms including patient database and inform consent
		4- Trial approval by the required organization or body
		5- Task distribution and training
**Phase 1**	**12 months**	1- Patient selection
		2- Randomization
		3- Administration of the trial treatment
		4- Patient evaluation (pre−/post-trial)
		5- Assessment of the target outcomes
		6- Evaluation of complications or adverse reaction, if any
		7- Analysis

## Methods/design

### Study type

This study will be a randomized controlled clinical trial.

#### Setting

Medani Tertiary Maternal Hospital in central Sudan.

### Patients

Inclusion criteria: women aged 18–40 years with a viable fetus diagnosed with threatened PTL and whose gestational age is between 25 and 34 weeks will be eligible for participation in this trial. A diagnosis of threatened PTL will be defined as persistent uterine contractions “(four contractions every 20 min or eight every 60 min)” with cervical changes “(cervical effacement ≤80% or cervical dilatation > 2 cm) [20]. Patients are eligible independent of the presentation of the fetus.Exclusion criteria: Women who have had multiple pregnancies; any condition considered as a contraindication for tocolysis, e.g., hypertension or the use of anti-hypertensive medication, ruptured membranes, signs of fetal distress and/or intrauterine infection; a maternal temperature > 38 °C; severe vaginal bleeding; myocardial infarction within 3 months; unstable angina pectoris; cervical dilatation of more than 5 cm; cerclage; suspicion of neonatal chromosomal or structural anomalies; tocolytic treatment for more than 6 h prior to arriving in the participating hospital; and an unwillingness to participate in this study.

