### Sample size

Each study group will consist of 117 women, a number calculated based on a previous study [17]. We expect the proportion of successful outcomes (the number of women who do not deliver and who do not need alternative treatment for 48 h) in nifedipine monotherapy to be 72.0%, and we expect it to be 89.0% in the combination group. This sample size (117 in each arm) was necessary to achieve a 95% confidence level with a 5% margin of error and 80% power.

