### Outcome measurements

#### Primary outcomes

The monitoring of uterine contractions will be performed continuously by an external tocodynamometer for 2–4 h after the first administration of the study’s medications followed by two to three times per day for 30–60 min. The primary outcome will be an estimation of the tocolytic effectiveness and safety profile. The effectiveness will be assessed in terms of the proportion of women who do not deliver and who do not need alternate tocolytic medication (terbutaline) within 48 h after the first administration of the study drug. Safety assessment will be performed by assessing maternal-associated adverse effects that include maternal tachycardia (i.e., a heart rate above 120 beats per minute), hypotension (i.e., systolic blood pressure less than 90 mmHg), and other symptoms, such as palpitations, headache, nausea, vomiting, itching, and rash.

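### As printed, the cervical entry threshold is met by a closed, uneffaced cervix, so it contradicts the cervical change it defines and could admit women without any

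*Protocol article*

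**What the plan says.** Protocol article, Patients: "A diagnosis of threatened PTL will be defined as persistent uterine contractions", at a frequency given as "four contractions every 20 min or eight every 60 min", and accompanied by cervical change. The change is specified in a parenthesis as "cervical effacement ≤80% or cervical dilatation > 2 cm".

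Protocol article, Abstract (Methods/design): the same parenthesis, with the same direction of inequality and the same alternative: "cervical effacement ≤80% or cervical dilatation >two cm".

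The only other cervical limit is an exclusion in Patients for "cervical dilatation of more than 5 cm". No exclusion covers a closed or uneffaced cervix.

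The effectiveness part of the primary outcome is "the proportion of women who do not deliver and who do not need alternate tocolytic medication (terbutaline) within 48 h" of the first study dose. Sample size expects success under "nifedipine monotherapy to be 72.0%, and we expect it to be 89.0% in the combination group", with 117 women per arm and 80% power.

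**The concern.** The parenthesis should turn the requirement for cervical change into something that screening staff can apply. Effacement increases as the cervix changes, so a criterion for change would be expected to set a floor. This one sets a ceiling. Read literally, it lets in the unchanged cervix and keeps out some women with marked effacement. Both places where the rule appears print it the same way, so a reader cannot correct one from the other.

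This is the diagnostic gate of the trial. Contracting women without cervical change may well remain undelivered at 48 h and need no terbutaline whichever regimen they receive. Each such woman adds a success to her arm without informing the comparison. Both success rates would then rise, the difference would shrink, and women without the intended diagnosis would receive trial drugs. Readers of the results could not tell from the stated criterion who had been enrolled.

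**Working it through.** **1. The rule as logic.** Let E be effacement (%) and D dilatation (cm). The printed cervical criterion is E ≤ 80 or D > 2. Its complement is E > 80 and D ≤ 2.

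| Cervix | E ≤ 80? | D > 2? | Printed criterion |
|---|---|---|---|
| Closed, uneffaced (E = 0, D = 0) | yes | no | met |
| E = 50, D = 1 | yes | no | met |
| E = 90, D = 3 | no | yes | met |
| E = 90, D = 2 | no | no | **not met** |

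The only women turned away on cervical grounds are those in the last row's category. The exclusion above 5 cm acts at the other end and does not affect the first row.

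**2. The plan's own sample size.** Inputs from Sample size: 72% and 89% success, 80% power, type I error 0.05. Sidedness is not stated, so I take it as two-sided. The mean rate is (0.72 + 0.89)/2 = 0.805.

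n = [1.96·√(2·0.805·0.195) + 0.842·√(0.72·0.28 + 0.89·0.11)]² / 0.17² ≈ 84.1, so 85 per arm, or 96 with continuity correction.

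The stated 117 is not reproduced. That is a separate matter. It is relevant here only because 117 gives more than 80% power on the stated rates.

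**3. Dilution.** Let f be the share of enrolled women without cervical change, and q their 48 h success rate, taken as equal in both arms. The documents give neither.

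- Monotherapy rate: (1 − f)·0.72 + f·q
- Combination rate: (1 − f)·0.89 + f·q
- Difference: 17·(1 − f) points, whatever q is

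Example with f = 0.20 and q = 0.90: 0.8·0.72 + 0.2·0.90 = 0.756, and 0.8·0.89 + 0.2·0.90 = 0.892, a difference of 13.6 points.

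**4. Power at 117 per arm.** This is Pearson's chi-squared test, two-sided 5%, without continuity correction. Exact power is the sum of the binomial probabilities of all outcome pairs that the test rejects.

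| f | Difference (points) | Power, q = 90% | Power, q = 100% |
|---|---|---|---|
| 0 | 17.0 | 92% | 92% |
| 20% | 13.6 | 79% | 83% |
| 30% | 11.9 | 70% | 77% |
| 50% | 8.5 | 45% | 61% |

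The normal approximation gives nearly the same picture: 91% with none, 78–82% at 20%, 69–76% at 30% and 45–59% at 50%.

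**The case against.** The strongest reply is that the inequality is only a parenthesis to a requirement that still stands. The definition asks for contractions at a stated frequency and for cervical change. A woman with an unchanged cervix meets the parenthesis but not the words it explains, and obstetric staff may well apply the intended rule. This stands. A reader might infer that the trial will enrol women without cervical change; the text permits that but does not establish it. What the reply cannot remove is the contradiction. An entry rule should not depend on staff disregarding its printed threshold.

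A second reply is that the loss of power is speculative and buffered. This also stands in part. Nothing in the document supports any particular share, and 117 per arm keeps power near the planned 80% even when a fifth of the women have no cervical change. The problem also does not favour either randomised arm; the harm is dilution and possible treatment of women without the diagnosis.

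Two further inferences are tempting and should not be drawn:

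- **That the 72% and 89% planning rates cannot apply.** They come from an earlier trial whose entry criteria are not given in the document. If that trial admitted a similarly broad group, its rates already reflect it.
- **That twins are admitted.** The exclusion "Women who have had multiple pregnancies" is awkwardly worded and could be read as obstetric history. But the same section speaks of a single viable fetus and of the presentation of the fetus, so exclusion of a current multiple gestation is the natural reading. This is a copy-edit, and no argument about correlated neonatal outcomes can rest on it.

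**Conclusion.** The point holds as an eligibility rule that is wrong as written. In both places where it is stated, the cervical threshold is satisfied by a closed, uneffaced cervix and fails only for effacement beyond 80% with dilatation of 2 cm or less. It contradicts the cervical change it is meant to define, and no other passage repairs it. This conclusion needs no assumption.

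The effect on the trial is conditional. If women without cervical change are enrolled, and mostly succeed at 48 h on either regimen, the difference falls to 17·(1 − f) points. The power figures rest on an assumed share, an assumed common success rate of 90–100%, and the plan's 72% and 89% holding in the remaining women. Up to a share of about 20% the planned power is roughly kept; at 30% or more it is not.

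**What to change.** Reconcile the effacement inequality with the requirement for cervical change, in Patients, in the Abstract and on the screening form, so that an unchanged cervix cannot qualify. The sponsor should check the wording against the definition it cites for this criterion. That source is not available here, so no discrepancy with it is claimed and no threshold is proposed.

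The cost is a change of eligibility wording and of the screening form. Enrolment may be slightly slower than under the literal criterion.

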**Fig. 1 Fig1:**
[figure not shown]
Patient recruitment flow chart

**Table 2 Tab2:**
[figure not shown]
Schedule of enrolment, interventions, and assessments during the clinical trial

### Sample size

Each study group will consist of 117 women, a number calculated based on a previous study [17]. We expect the proportion of successful outcomes (the number of women who do not deliver and who do not need alternative treatment for 48 h) in nifedipine monotherapy to be 72.0%, and we expect it to be 89.0% in the combination group. This sample size (117 in each arm) was necessary to achieve a 95% confidence level with a 5% margin of error and 80% power.

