## Discussion

We are expecting a higher effectiveness of the combination indomethacin/nifedipine tocolytic therapy compared with nifedipine monotherapy. Among the various tocolytics, nifedipine seems to be the most appropriate therapy for PTL [15]. However, it has been suggested that combination therapy is a good option for postponing of PTL [16]. Our findings will be supported by the recent findings of Kashanian et al. who enrolled 150 participants; these investigators reported that 89.4% of the combination-therapy patients compared to 72.0% of the patients in either a nifedipine or indomethacin monotherapy group had inhibition of uterine contractions for 48 h. Accordingly, the investigators indicated combination therapy be employed for inhibiting preterm labor, delaying delivery, and prolonging the duration of pregnancy [17].

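### The protocol describes the 72% and 89% behind the sample size as two different events, so the stated 80% power is not shown for the primary endpoint; at those rates 117 per arm gives about 91–92%.

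*Protocol article*

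**What the plan says.** The Sample size section bases 117 women per arm on one previous trial (reference 17). It defines success there as the trial's own endpoint: "We expect the proportion of successful outcomes (the number of women who do not deliver and who do not need alternative treatment for 48 h". It expects success "in nifedipine monotherapy to be 72.0" per cent, and "we expect it to be 89.0% in the combination group". It says that 117 per arm "was necessary to achieve a 95% confidence level with a 5% margin of error and 80% power". The Abstract says the number is set "according to a type I error of 0.05 and a study power of 80" per cent.

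Under Primary outcomes, effectiveness is "the proportion of women who do not deliver and who do not need alternate tocolytic medication (terbutaline) within 48 h" of the first dose. This agrees with the label in the Sample size section.

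The Discussion cites the same reference and describes its result differently. It gives 89.4% for the combination, against "72.0% of the patients in either a nifedipine or indomethacin monotherapy group had inhibition of uterine contractions for 48 h".

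The Interventions section connects the two events. Terbutaline is the second-line drug for unsuccessful treatment in both arms, provided it is not contraindicated. The Blinding section says the trial is open.

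**The concern.** The control rate is the same in both places (72.0%), the combination rates differ only by 0.4 points (89.0% and 89.4%), and the source is the same. Yet one section calls the event freedom from delivery and rescue, and the other calls it contraction inhibition.

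The two events can classify the same woman differently. If her contractions persist, she is not given terbutaline and she has not delivered by 48 h, she fails on inhibition but succeeds on the primary endpoint. If she delivers or is rescued although her contractions were recorded as inhibited, the reverse holds.

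If the Discussion's description is the correct one, the protocol has no planning rates for the endpoint it will test. The 17-point difference and the 80% power would then rest on the two events giving nearly the same rates, which the document does not argue.

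**Working it through.** **Inputs.** Success 72.0% and 89.0%, 117 per arm, 1:1, alpha 0.05 and power 80%, all from the Sample size section and the Abstract. The article does not state sidedness; a two-sided test is assumed. The Analysis section names Pearson's chi-squared test.

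**Step 1: the plan's own figure.** With pooled rate p̄ = (0.72 + 0.89)/2 = 0.805 and Δ = 0.17,

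n = [1.96·√(2p̄(1−p̄)) + 0.842·√(p₁(1−p₁) + p₂(1−p₂))]² / Δ²

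This gives 84.1, so 85 per arm, or 96 with continuity correction. With 89.4% in place of 89.0% it gives 80, or 91 with continuity correction. The stated inputs do not reproduce 117.

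**Step 2: power of 117 per arm at the stated rates.**

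- SE under the null: √(2 × 0.805 × 0.195/117) = 0.0518.
- SE under the alternative: √((0.72 × 0.28 + 0.89 × 0.11)/117) = 0.0506.
- Power = Φ((0.17 − 1.96 × 0.0518)/0.0506) = Φ(1.35) = 91.2%.
- Exact enumeration for the uncorrected Pearson chi-squared test gives 92.0%.

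So the plan has slack at its stated rates, and 80% is not the power that 117 per arm provides there.

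**Step 3: what happens if the rates are inhibition rates.** The document gives no figure for how often the two events disagree. Two one-parameter assumptions show the sensitivity; each fraction is taken as equal in both arms.

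*Assumption A.* A fraction f of inhibition failures are neither delivered nor rescued within 48 h. Failure rates on the endpoint become 0.28(1−f) and 0.11(1−f).

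| f | Failure, mono vs combination | Power, normal approx. | Power, exact Pearson |
|---|---|---|---|
| 0 | 28.0% vs 11.0% | 91.2% | 92.0% |
| 0.10 | 25.2% vs 9.9% | 87.3% | 88.3% |
| 0.20 | 22.4% vs 8.8% | 82.2% | 83.4% |
| 0.25 | 21.0% vs 8.25% | 79.2% | 80.4% |
| 0.50 | 14.0% vs 5.5% | 59.3% | 61.5% |

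*Assumption B.* A fraction e of inhibited women are still delivered or rescued. Failure rates become 0.28 + 0.72e and 0.11 + 0.89e.

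| e | Failure, mono vs combination | Power, normal approx. | Power, exact Pearson |
|---|---|---|---|
| 0.05 | 31.6% vs 15.5% | 83.4% | 83.8% |
| 0.07 | 33.0% vs 17.2% | 80.0% | 80.3% |
| 0.10 | 35.2% vs 19.9% | 74.8% | 75.1% |

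The slack from Step 2 absorbs disagreement up to about a quarter of inhibition failures, or about 7% of inhibited women. Beyond that, power is below 80%.

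**The case against.** The strongest reply is that the conflict may be one of wording only. The Discussion gives a one-sentence paraphrase. The previous trial may have reported both outcomes, or may have defined inhibition as no delivery and no rescue. A reader might infer that the Methods label is the error and the Discussion has the true definition. The document does not support that: it contains two descriptions and nothing that decides between them. This part of the reply stands.

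The second reply is that the Interventions section makes the events largely coincide. Treatment that fails to inhibit contractions normally leads to terbutaline, and so to failure on the primary endpoint. Rescue of a woman whose contractions are inhibited is not a written route at all. This also stands, and it argues against large values of f and e. It does not make the events identical. Terbutaline is withheld where contraindicated, rescue is decided by staff who know the arm, and delivery is a separate component.

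The third reply is that the break points are soft. On the exact Pearson test, power is still 80.4% at f = 0.25 and 80.3% at e = 0.07. That is correct, and both calculations are shown above.

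A reader might also want contraction inhibition for 48 h added as an outcome, since tracings are taken anyway: "The monitoring of uterine contractions will be performed continuously by an external tocodynamometer for 2–4 h after the first administration". After that period, however, recording is only two to three times a day for 30–60 min, so such traces cannot directly show inhibition over 48 h. Matching an earlier trial's measure is a preference, not a requirement for this trial's validity.

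**Conclusion.** The point holds as an unresolved contradiction with a consequence for the stated power. One pair of rates from one source is described as two different events, and only one of those is the primary endpoint. The single 80% figure is therefore not supported for that endpoint.

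It would be tempting to conclude that the trial is underpowered. The document does not support this. If the Sample size label is right, 117 per arm gives about 91–92%, well above the claim. If the Discussion is right, power depends on how often the events disagree: 82–83% at f = 0.20 and 59–61% at f = 0.50, or 83–84% at e = 0.05 and 75% at e = 0.10. The document gives neither fraction, so a fall below 80% is possible but not shown.

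The stated 80% is also wrong as arithmetic at the plan's own rates, whichever description is correct. All power figures assume a two-sided test at 0.05, 117 analysed per arm and, in the sensitivity range, equal disagreement fractions in both arms.

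**What to change.** 1. Reconcile the Sample size section and the Discussion by stating which outcome of the previous trial the 72.0% and 89.0%/89.4% describe. If that trial reports rates for no delivery and no rescue within 48 h, use those for planning.
2. Replace the single 80% with the power of 117 per arm: about 91–92% at 72% versus 89%, two-sided 0.05.
3. Unless step 1 yields rates for the trial's own endpoint, add a sensitivity range with its assumptions labelled. For inhibition failures neither delivered nor rescued: 82–83% at 20%, 79–80% at 25%, 59–61% at 50%. For inhibited women still delivered or rescued: 83–84% at 5%, 80% at 7%, 75% at 10%.

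The cost is a check of the cited paper and a rewording of one paragraph and one sentence. No additional patients, procedures or outcomes are needed. The downside is that the stated power becomes a range, part of which is below 80%.

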### Analysis

Statistical analysis will be performed by using the SPSS version 22.0 (IBM) program (intention-to-treat analysis). In the evaluation of the study data, descriptive statistical methods (mean, standard deviation, minimum, maximum, median, frequency, and ratio) will be used. Student’s *t*-test will be used to compare quantitative data for normally distributed data, and if the distribution is not consistent with a normal distribution, the Mann–Whitney *U* test will be used to compare the variables between women in each arm of the study. Pearson’s chi-squared and Fisher’s exact tests will be used for qualitative data comparisons. Number needed to treat (NNT) for benefits and number needed to harm (NNH) for adverse outcomes with their 95% confidence outcomes will be calculated. A *p*-value> 0.05 will be considered statistically significant.

The groups (nifedipine/indomethacin combination group or nifedipine monotherapy group) will be analyzed as group A and group B, and confidentiality will be preserved. The identification of groups will be revealed only after the analysis is finished with the tables ready.

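### The printed inputs (72.0% vs 89.0%, alpha 0.05, 80% power) give 82 to 96 women per arm, not 117; at 117 the power is about 90%, and the 5% margin of error is not an input to this calculation

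*Protocol article*

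**What the plan says.** The Sample size section of the protocol article bases its number on an earlier trial. It expects success (no delivery and no alternative treatment for 48 hours) "in nifedipine monotherapy to be 72.0%, and we expect it to be 89.0% in the combination group". It then states: "This sample size (117 in each arm) was necessary to achieve a 95% confidence level with a 5% margin of error and 80% power".

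The Methods/design part of the abstract gives the same 117 per arm, "according to a type I error of 0.05 and a study power of 80" per cent, and mentions no margin of error. Neither place states sidedness, a continuity correction or an allowance for losses. For categorical outcomes the Analysis section names Pearson's chi-squared test and Fisher's exact test.

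**The concern.** The article prints every quantity that a two-proportion sample size needs except sidedness, and it calls the result necessary for 80% power. A reader should therefore be able to reproduce 117, and the standard formulas fall well short of it.

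The sentence also lists a margin of error beside the power. A margin of error is a precision target for an estimate; it does not enter a power calculation for comparing two proportions. If a reader takes it at face value, the article promises an interval far narrower than the trial will deliver.

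At stake are the two figures that readers use to judge what the trial can show: its power for the planned effect, and the precision of its estimate. This paragraph is also the article's only justification for enrolling 234 women (2 × 117).

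**Working it through.** **Inputs.** p1 = 0.72 and p2 = 0.89 (Sample size section); alpha = 0.05 and power = 80% (abstract and Sample size section); equal arms of 117. Two-sided testing is my assumption, because sidedness is not stated. Then d = 0.17, the mean rate is p̄ = 0.805, z(0.975) = 1.960 and z(0.80) = 0.842. The variance terms are p1(1−p1) + p2(1−p2) = 0.2016 + 0.0979 = 0.2995 and 2p̄(1−p̄) = 0.31395.

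**Step 1. Attempt to reproduce 117 at 80% power.**

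- Unpooled variance: (1.960 + 0.842)² × 0.2995 / 0.17² = 7.849 × 0.2995 / 0.0289 = 81.3, so 82 per arm.
- Pooled variance under the null, unpooled under the alternative (Fleiss): (1.960 × √0.31395 + 0.842 × √0.2995)² / 0.0289 = (1.0982 + 0.4606)² / 0.0289 = 84.1, so 85.
- Pooled variance throughout: 7.849 × 0.31395 / 0.0289 = 85.3, so 86.
- Arcsine: 82.
- Fleiss with continuity correction: (84.08 / 4) × [1 + √(1 + 4 / (84.08 × 0.17))]² = 21.02 × (1 + 1.1313)² = 95.5, so 96.

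One-sided testing moves away from 117: it needs 65 to 68 per arm, or 78 with continuity correction. The closest variant of the printed inputs is 96, which is 21 women per arm below 117.

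**Step 2. Power at 117 per arm for 72.0% vs 89.0%, two-sided 0.05.**

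- Normal approximation: (0.17 × √117 − 1.960 × √0.31395) / √0.2995 = (1.8388 − 1.0982) / 0.5473 = 1.353, which gives 91.2%.
- Exact enumeration over both binomial distributions: 92.0% for Pearson's chi-squared and 89.1% for Fisher's test.

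**Step 3. Effect detectable with 117 per arm at 80% power.** With p1 = 0.72 and no continuity correction, the same normal approximation gives 79.7% at p2 = 0.867 and 80.3% at p2 = 0.868. So 80% power corresponds to about 72% vs 86.7%, a difference of about 14.7 points rather than 17.

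**Step 4. The 5% margin of error, read literally.** The 95% half-widths at 117 per arm are:

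| Quantity | Half-width |
|---|---|
| 72% arm | 1.96 × √(0.2016 / 117) = ±8.1 points |
| 89% arm | 1.96 × √(0.0979 / 117) = ±5.7 points |
| Difference | 1.96 × √(0.2995 / 117) = ±9.9 points |

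None of these reaches 5 points.

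**The case against.** The strongest reply is that 117 includes an allowance for losses that the condensed article leaves out. The arithmetic permits this: 96 / (1 − 0.18) = 117.1, so about 18% loss on the continuity-corrected figure fits. In that case the rates and the 80% could both be right. This stands as a possible explanation, and leaving such an allowance to a fuller document is not an error in itself. It does not rescue the sentence as printed, which attributes 117 to the confidence level, margin and power alone.

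A second reply is that the margin of error is only the type I error misnamed, since the abstract gives 0.05 as the type I error for the same 117. I accept that as the likely reading. A 5-point precision target was then never intended, and the phrase is a wording slip.

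A third reply is that the discrepancy does no harm. It does run in the safe direction: more women than the stated power requires.

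A reader might go further and infer that the stated power or rate must be wrong, because 72.0% vs 89.4% at 90% power with continuity correction gives 117.2. The documents do not support that inference. Rounded up, 117.2 is 118. Other unstated inputs also reach 117: the loss allowance above, or 72% vs 87.5% at 80% power with continuity correction (116.9). Nothing shows which route, if any, was used.

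A reader might also object to the 89.4% in the Discussion ("89.4% of the combination-therapy patients compared to 72.0% of the patients in either a nifedipine or indomethacin monotherapy group"). That is the earlier trial's result, and planning on 89.0% is ordinary, slightly cautious rounding. The Discussion describes that result as inhibition of contractions, but a one-line paraphrase of a study not at hand cannot establish that its endpoint differed from this trial's.

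**Conclusion.** The point holds as a reporting error. At two-sided alpha 0.05, 72.0% vs 89.0% with 80% power needs 82 to 86 women per arm, or 96 with continuity correction, so 117 was not necessary for the stated power on the stated inputs. At 117 per arm the power is about 89% to 92%, depending on the test. The margin of error is a misplaced term; taken literally, it would be about half the expected half-width of ±9.9 points for the difference.

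These figures assume two-sided testing, the two planning rates as printed, and outcome data for all 117 women per arm. If losses were expected, the power at the analysed number would be lower. The documents do not show whether the power, a rate or an omitted allowance is the source of the mismatch; the supportable statement is that the printed inputs and the printed number disagree.

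This should be fixed but is not critical: on its own assumptions the trial is not underpowered, and the planned tests are unaffected.

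**What to change.** Keep 117 per arm. In both the abstract and the Sample size section, do one of the following:

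- Restate the power: 117 women per arm give about 90% power for 72.0% vs 89.0% at two-sided alpha 0.05.
- If 117 was reached another way, state that basis, with the formula, any continuity correction and any loss allowance. A loss of about 18% on a continuity-corrected 96 would be one such basis, but only if the sponsor confirms that it was intended.

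In the Sample size section, replace the margin-of-error phrase with a two-sided type I error of 5%. If a statement on precision is wanted, give the expected 95% half-width for the difference, about ±10 points.

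The cost is rewording in two places. Enrolment, randomisation and analysis do not change.
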